#### Procedures for Recording AEs

Dexamethasone is an established and commonly used drug with a well-characterized toxicity profile. All AEs (grades 3‐4) will be recorded and reported. Mild and moderate AEs (grades 1‐2) will be recorded only if the investigator considers that the AE is definitely, probably, or possibly related to the study drug. All SAEs will be recorded and reported. If all the information required to report the event is not available initially, the SAE may first be recorded as an initial report, with follow-up and final reports recorded as needed. All AEs, serious and nonserious, will be recorded during the 28-day trial period.

The following information will be recorded: description, onset date and end date, severity, assessment of relatedness to the trial medication, other suspect drug or device, and action taken. Follow-up information should be provided as necessary. All AEs will be followed until resolution or until the event is considered stable.

The investigator will decide whether an AE is sufficiently severe to require the participant’s removal from treatment. A participant may also voluntarily withdraw from treatment because of what he or she perceives as an intolerable AE. If either of these occurs, the participant will undergo an end-of-trial assessment and receive appropriate care under medical supervision until symptoms cease, or the condition becomes stable.

All SAEs will be reported to the IEC within 24 hours of becoming aware of the SAE, and a detailed report will be submitted within 14 days of the event.

### Ethical Considerations

#### Screening, Informed Consent, and Enrollment

Study team members, trained at each site, will screen all near-hanging patients with altered sensorium presenting to participating emergency departments for eligibility. As these patients have impaired consciousness, informed consent will be obtained from their legally acceptable representative (LAR), who will receive a clear explanation of the study objectives, procedures, benefits, and risks and will have all questions answered before providing written consent, which will be countersigned by the investigator responsible for recruitment. Patients will be reconsented once they regain full consciousness (GCS 15/15). All screened patients will receive a unique screening ID, with exclusion reasons documented for noneligible cases; enrolled patients will receive a separate enrollment number for procedures and follow-up. To ensure standardized data tracking and patient confidentiality, a Unique Patient Identifier (UI) system will be used. Each center will use its 2-letter alpha code (JI, IG, or PG) followed by an “S“ for Screening or an “E“ for enrollment and then a 3-digit serial number (eg, 001, 002, and so on). For example, JIS006 identifies the sixth patient screened at the JIPMER site, while JIE003 identifies the third patient enrolled at the same site.

#### Ethical Approval

This clinical trial is conducted in accordance with the principles in the latest version of the Declaration of Helsinki. This trial was approved by the Institutional Ethics Committee of the lead site, JIPMER, Puducherry, India, dated January 22, 2025. The other sites subsequently obtained approval from their respective ethics committees (IGMCRI, Puducherry, India, on April 8, 2025, and PGIMER, Chandigarh, India, on August 26, 2025).

#### Ethical Issues

Patients or their attendants may be in a state of emotional distress after a suicide attempt. We will address this issue carefully. All participating sites submitted the study protocol, patient information sheet, and consent forms to their local ethics committee for approval. The patient information sheet and consent forms have been translated into the relevant regional languages and back translated into English to ensure the accuracy of the translation. Consent is initially obtained from the patient’s attendant, the LAR, as the patient will be unconscious. Later, once the patient regains consciousness, reconsent is obtained from the patient. The patient or the LAR is also given the opportunity to withdraw from the study at any time. The principal investigator has purchased clinical trial insurance using the allocated funds to ensure compensation for participants for any foreseeable and unforeseeable risks arising from the study.

### Trial Registration

This trial has been registered with the Clinical Trials Registry India (CTRI/2025/02/081343) on February 25, 2025. Patient recruitment commenced on October 3, 2025.

### Data Safety and Monitoring Board

Given the interventional nature of this trial, an independent Data and Safety Monitoring Board (DSMB) has been constituted in accordance with JIPMER’s DSMB guidelines to oversee participant safety and trial conduct. A DSMB charter was developed prior to trial initiation. The charter details the composition of the committee, minimum quorum requirements, frequency of meetings, the structure of meetings (open and closed sessions), and the procedures for documentation, communication, and reporting of recommendations.

The DSMB comprises 3 independent members: one expert from each of emergency medicine, internal medicine, and biostatistics. A quorum of 2 members is required for DSMB meetings. The study statistician will be responsible for presenting the interim efficacy analyses, and a consolidated summary of all AEs and SAEs will be submitted for DSMB review. The DSMB will periodically review accumulated safety and efficacy data, including a planned interim review after 50% enrollment in each treatment arm. Based on its evaluation, the DSMB may recommend continuation of the study without modification, protocol modification, or early termination of the trial. All DSMB recommendations will be formally communicated to the principal investigator, who will subsequently report them to the Institutional Ethics Committee.

An interim analysis will be conducted after enrollment of 50% of the planned sample size. The Haybittle-Peto stopping rule will be applied, with statistical significance for early termination defined as a *P* <.002 at the interim analysis stage. However, the final analysis will retain a 2-sided *α* level of .05.

### Monitoring Sites During the Study

The coordinating center will monitor the study and ensure compliance with the protocol, Good Clinical Practice guidelines, and relevant regulatory requirements. A checklist has been created to ensure the readiness of each site to start patient recruitment. A site initiation meeting will be held via an online platform, and study investigators from the primary center will conduct a site visit to ensure that sites are equipped and able to run the trial. In addition, the lead center will conduct regular online meetings to ensure compliance with the study protocol and the integrity of the study data.

### Disseminating the Study Results

The results of the trial will be disseminated through publication in a peer-reviewed journal so that the scientific community can use the conclusions of this study to manage patients better. Authorship will be based on contributions to the study. Following completion of the study, the principal investigator will have access to the final dataset.

### Data Analysis Plan

#### Summary Statistics

Continuous data will be expressed as the mean and SD, or the median with an IQR. Categorical data will be expressed as percentages. The independent variables in the study include both continuous and categorical factors. Continuous independent variables are age, mean arterial pressure, GCS at admission, time interval between the incident and presentation, admission blood glucose level, and GOS at discharge and on day 28. The categorical independent variables include sex, type of hanging (complete or partial), material used for hanging, presence of seizures, hanging-induced cardiac arrest, requirement for mechanical ventilation, vasopressor support, and in-hospital complications. The dependent variables consist of both continuous and categorical outcomes. The continuous dependent variable is the duration of hospital stay, while the categorical dependent variables include the proportion of patients with a good neurological outcome at discharge and on day 28, as well as the occurrence of in-hospital complications.

#### Analytical Statistics

The primary and secondary outcomes will be compared between the intervention and placebo groups using appropriate statistical tests. The proportion of patients achieving good neurological outcomes on day 28, as well as the proportion achieving good neurological outcomes at discharge, will be analyzed using the chi-square or Fisher exact test, with results expressed as relative risk estimates. Similarly, the comparison of in-hospital complications between the 2 groups will also use the chi-square or Fisher exact test, with relative risk used to quantify the effect size. For continuous outcomes, such as the duration of hospital stay, comparisons will be made using either the independent *t* test or the Mann-Whitney *U* test depending on data distribution, and the effect will be reported as an absolute difference between groups.

The primary efficacy analysis will be carried out by following the intention-to-treat principle. A per-protocol analysis will be performed as a secondary analysis. If there are missing data for the outcome at day 28, multiple imputation using chained equations will be used, based on the assumption that data are missing at random [26]. The primary analysis will also adjust for GCS stratification at baseline using a multivariable regression model. No adjustment for study site will be carried out, as all the sites have a similar profile with respect to available treatment and manpower. All statistical analyses will be carried out at a 5% level of significance, and a *P* value <.05 will be considered significant. For interim analyses alone, *P*<.002 will be applied, following the Haybittle-Peto stopping rule.

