**Methods:**

The CHANGING trial (Corticosteroids in HANGING) is a multicenter, double-blind, randomized, placebo-controlled study at 3 Indian tertiary centers. It enrolls 192 near-hanging patients with a Glasgow Coma Scale score ≤13 over 3 years, randomizing them in a 1:1 ratio to IV dexamethasone or placebo, plus standard care for 3 to 5 days. The primary outcome is neurological recovery at day 28, assessed using the Glasgow Outcome Scale. Secondary outcomes include the Glasgow Outcome Scale at discharge, duration of hospital stay, and the incidence of in-hospital complications. This trial has been approved by Jawaharlal Institute of Postgraduate Medical Education and Research, Puducherry Institute Ethics Committee (January 22, 2025), with subsequent approvals from Indira Gandhi Medical College and Research Institute (April 8, 2025) and Postgraduate Institute of Medical Education and Research (August 26, 2025).

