### Randomization and Allocation Concealment

Central randomization will be conducted at the coordinating center. Participants will be randomly allocated in a 1:1 ratio to receive either intravenous dexamethasone or placebo using a computer-generated randomization sequence. Variable block sizes of 4 and 6 will be used, with stratification based on baseline GCS score (≤8 and >8) to ensure balance between the treatment groups. Allocation concealment will be ensured using the Sequentially Numbered Opaque Sealed Envelopes method.

The study medications (dexamethasone or placebo) are prepared in identical-looking vials and labeled with a 5-character alphanumeric code using a randomly generated sequence, as shown in Figure 2. They are securely packed in designated boxes for each site. The random sequence used for labeling the study medications is stored in a password-protected Microsoft Excel sheet, accessible only to an unblinded investigator at the primary site to ensure confidentiality and maintain blinding throughout the study.

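### The secondary outcomes are compared without the GCS stratum used in randomization, which costs some power if GCS clearly predicts them

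*Protocol article*

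**What the plan says.** All references are to the protocol article.

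- **Randomization and Allocation Concealment.** Allocation is 1:1 in permuted blocks: "Variable block sizes of 4 and 6 will be used, with stratification based on baseline GCS score (≤8 and >8"). The stated aim is balance between the arms.
- **Abstract, Methods.** "Secondary outcomes include the Glasgow Outcome Scale at discharge, duration of hospital stay, and the incidence of in-hospital complications".
- **Analytical Statistics, good outcome at discharge.** This outcome, "as well as the proportion achieving good neurological outcomes at discharge, will be analyzed using the chi-square or Fisher exact test", is reported as a relative risk.
- **Analytical Statistics, complications.** "Similarly, the comparison of in-hospital complications between the 2 groups will also use the chi-square or Fisher exact test", again with a relative risk.
- **Analytical Statistics, hospital stay.** Here "comparisons will be made using either the independent *t* test or the Mann-Whitney *U* test depending on data distribution", reported as an absolute difference.
- **Analytical Statistics, use of the stratum.** "The primary analysis will also adjust for GCS stratification at baseline using a multivariable regression model". No sentence extends this to a secondary outcome.

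The same section sets a 5% significance level for all analyses other than the interim. The Subgroup Analysis section lists the same GCS split as a measure of neurological severity.

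**The concern.** Blocked randomization within GCS strata makes the arms nearly equal in their GCS mix. Differences between strata therefore contribute almost nothing to the chance variation of the arm comparison. A test that ignores the stratum still counts those differences in its standard error. If the stratum is prognostic, the standard error is too large: the true type I error falls below 5%, intervals are too wide and power is lost.

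The design and the primary analysis both treat GCS as important, while the secondary tests leave it out. The named tests are a stated choice, not a detail left open. What is at stake is precision on three secondary outcomes in a trial whose size is limited by feasibility (Sample Size section: 190 to 200 eligible patients expected). One of these outcomes, complications, is the comparison most relevant to steroid harm.

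**Working it through.** **1. The plan's own figure.** The Sample Size section assumes 75% vs 55% good outcome and 80% power.

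n = (z₀.₉₇₅ + z₀.₈₀)² × (0.75×0.25 + 0.55×0.45) / 0.20² = 7.849 × 0.435 / 0.04 = 85.36, so 86 per arm; 86 / 0.90 = 95.6, so 96.

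Both stated figures reproduce with α = 5%. (The section prints α as 0.05%, which taken literally would give 204 per arm.) The check below uses 86 per arm, 172 in total.

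**2. Approximate size for a binary outcome.** The article gives no rates by stratum, so these are assumed: half of the patients in each stratum, overall placebo rate 55%. With exact balance, the crude standard error is too large by k = √(V_total / V_within), where V_total = 0.55×0.45 = 0.2475 and V_within is the mean of p(1−p) over the two strata. The true type I error is about 2[1 − Φ(1.96k)].

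| Placebo rate, GCS ≤8 / >8 | V_within | k | Approximate true α |
|---|---|---|---|
| 50% / 60% | 0.2450 | 1.005 | 4.9% |
| 40% / 70% | 0.2250 | 1.049 | 4.0% |
| 30% / 80% | 0.1850 | 1.157 | 2.3% |

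**3. Simulation for a binary outcome.** 200,000 trials per scenario, equal and balanced strata, common odds ratio chosen to move the overall rate from 55% to 75%. Each cell gives crude chi-square / Mantel-Haenszel.

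| Placebo rates | Type I error | Power | Gain in power |
|---|---|---|---|
| 50% / 60% | 5.4 / 5.4% | 79.1 / 79.4% | 0.3 points |
| 40% / 70% | 4.5 / 5.0% | 79.9 / 82.5% | 2.6 points |
| 35% / 75% | 3.7 / 5.1% | 80.6 / 84.9% | 4.3 points |
| 30% / 80% | 2.6 / 5.0% | 81.6 / 87.8% | 6.2 points |

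The simulated crude levels lie a little above the approximation because counts are discrete. A separate simulation with the actual blocks of 4 and 6 (6,000 trials per scenario) agrees. At 40/70% it gives type I error 4.7 / 5.2% and power 79.9 / 82.1%; at 30/80%, 2.8 / 4.7% and 80.9 / 87.1%. With unequal strata (40% of patients in GCS ≤8, rates 25/75%), it gives 2.7 / 5.1% and 82.4 / 88.8%. The stratified test lost no power in any scenario.

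**4. Complications.** The article states no complication rate, so all rates here are assumed (172 patients, equal strata). With a common odds ratio of 2.0 or 2.5, the gain in power from stratifying is:

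| Placebo complication rate, GCS ≤8 / >8 | Gain in power |
|---|---|
| 30% / 20% | under 1 point |
| 40% / 20% | about 1 to 2 points |
| 25% / 10% | about 1.5 to 2 points |
| 35% / 15% | about 2.5 points |
| 50% / 20% | about 2 to 3 points |
| 50% / 10% (extreme) | about 10 points |

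If the overall rate instead rises from 30% to 50%, placebo rates of 45/15% give type I error 3.9 / 5.1% and power 78.9 / 82.2%, a gain of 3.3 points. Rates of 50/10% give power 80.4 / 86.6%, a gain of 6.2 points. At an odds ratio of 2.0, power is about 44 to 57% under either test outside the 50/10% case.

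**5. Hospital stay.** For a continuous outcome with a share R² of its variance explained by the stratum, k = 1/√(1 − R²). If the adjusted test has 80% power:

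| R² (assumed) | Interval wider by | True α, unadjusted | Power, unadjusted |
|---|---|---|---|
| 0.05 | 2.6% | 4.4% | 78.5% |
| 0.10 | 5.4% | 3.9% | 76.9% |
| 0.20 | 11.8% | 2.8% | 72.9% |

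This describes the t test; the Mann-Whitney test was not computed.

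**The case against.** **Efficiency only.** The error is conservative, the primary outcome already carries the adjustment, and the trial is sized on day-28 outcome alone, so no secondary outcome has a stated power to fall short of. This stands, and it limits the priority of the point.

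**Size rests on assumption.** No outcome is reported by GCS stratum, and in the mildest scenario nothing is lost. This stands, so the point is conditional on GCS being clearly prognostic.

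**Scope of the adjustment.** The adjustment sentence follows the contrast between intention-to-treat and per-protocol analyses, so the primary analysis could mean the intention-to-treat analysis of every outcome. The day-28 primary outcome is the plainer reading. If the wider meaning is intended, one clarifying sentence is still needed.

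**A fuller plan may adjust.** A statistical analysis plan not shown could add adjusted secondary analyses. This counts only in part, because the article itself names the tests. The planned GCS subgroup analyses will give results within each stratum, but not a pooled stratified comparison.

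**Two stronger readings are not supported.**

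- A reader might infer that the discharge and day-28 results could not be compared because one is crude and the other adjusted. The article gives both outcomes the same crude test and relative risk, and then says the primary analysis will *also* be adjusted. Crude relative risks will therefore exist at both times.
- A reader might infer that the crude test could hide a real steroid harm. Outside an extreme split, the loss for complications is a few points at most, and power for an odds ratio of 2.0 is only about 44 to 57% under either test. Sample size limits the harm comparison far more than the missing stratum does.

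**Conclusion.** The point holds as a modest, conditional loss of efficiency. The article stratifies randomization by GCS and names only unstratified tests for the three secondary outcomes. If GCS clearly predicts these outcomes, the tests run below 5% and lose some power, without bias or excess false positives.

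For good outcome at discharge, the loss is practically nil for a 10-point difference between strata, about 2 to 3 points of power for 30 points and about 6 points for 50 points. For complications it is mostly about 0.5 to 3 points, which is a small loss of sensitivity to harm. For hospital stay it is about 1.5 to 7 points over R² of 0.05 to 0.20 (80 − 78.5 and 80 − 72.9).

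These figures assume 86 analysed per arm, roughly equal strata and a common odds ratio. The discharge figures also borrow the 55% and 75% that the article gives for day 28. The stratum rates, the complication rates and R² are all assumed.

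**What to change.** In Analytical Statistics, extend the GCS-stratum adjustment from the primary analysis to the secondary comparisons:

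- **Good outcome at discharge and in-hospital complications:** a Mantel-Haenszel relative risk stratified by GCS ≤8 vs >8, or a modified Poisson model with arm and stratum. Both keep the relative risk already planned.
- **Hospital stay:** a van Elteren test (the stratified counterpart of the Mann-Whitney test), or a linear model with arm and stratum, which keeps the absolute difference.

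The crude results may be kept as descriptive. If the existing adjustment sentence was meant to cover all outcomes, say so explicitly.

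The cost is one sentence. The stratum is known for every participant at randomization, so no new data or patients are needed. Only 3 patients had been enrolled when the article was submitted, so the change can be made well before any analysis.

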### Objectives

The primary objective of this study is to evaluate the efficacy of intravenous dexamethasone, compared with placebo, in achieving a good neurological outcome (Glasgow Outcome Scale [GOS] 4‐5) at day 28 in patients presenting with near-hanging with altered sensorium. Secondary objectives are to assess neurological outcomes at hospital discharge, compare the length of hospital stay, and compare the incidence of in-hospital complications between the dexamethasone and placebo groups.

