**Exclusion criteria**
Concurrent use of other methods of suicide.Active tuberculosis, HIV infection, recent systemic steroid use, other immunosuppressive therapy, or any definite indication or contraindication to corticosteroid therapy.Known hypersensitivity to dexamethasone or study-related drugs.Pregnancy or breastfeeding.Pre-existing neurological disorders.Hanging-related cervical spine injury.Moribund state where survival is deemed unlikely irrespective of intervention.

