### Assessment at Discharge

The outcome assessment will include the GOS at discharge (shown in Table 3) [24]. We will also assess the duration of study medication, whether full sensorium is achieved during hospitalization, and the time taken to achieve full sensorium (defined as a GCS score of 15 maintained for more than 24 h). Additional outcomes will include the duration of hospital stay and intensive care unit stay, the need for ventilatory support, including its duration and type, and the requirement for vasoactive support and its duration, if applicable. All AEs, as defined in the study protocol, will be documented. For participants who do not complete the study, the reasons for noncompletion will be recorded in detail.

**Table 3. T3:** Glasgow Outcome Scale (GOS) for neurological outcome [24].

GOS score	Rating	Description	Outcome category
1	Death	Death	Poor
2	Persistent vegetative state	Patient unresponsive and speechless for weeks or months	Poor
3	Severe disability	Dependent for daily support	Poor
4	Moderate disability	Disabled but independent	Good
5	Good recovery	Resumption of normal life with minor neurological and psychological deficits	Good

### Outcome Assessment on Day 28

The patient will be called for a follow-up on day 28 to assess GOS. The outcome will be assessed by the study staff who are blinded to the treatment allocation. If the patient cannot attend in person, GOS will be ascertained by telephone or video call. A standardized, structured interview process will be followed during the outcome assessment. Participants who die before day 28 will be assigned a GOS of 1 and will be included in the primary outcome analysis.

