## Discussion

### Expected Findings

The hypoxic-ischemic brain injury seen in near-hanging is associated with substantial mortality and long-term neurological disability despite advances in critical care [5,7]. The secondary brain injury determines the neurological outcome despite prompt resuscitation. Jugular venous obstruction results in flow stagnation, leading to cerebral hypoxia, which may be the initial event in hanging. Excessive cerebral perfusion of an already hypoxic brain following relief of obstruction may also contribute to cerebral edema [5,21]. Currently, there is no guideline-directed therapy for improving neurological recovery in these patients, and the management is only supportive [21].

The pathophysiology of cerebral edema in near-hanging is poorly understood. The following mechanism is proposed for hypoxia-induced cerebral edema at high altitudes and in traumatic brain injury. Hypoxia at altitude elicits neuro-hormonal (VEGF, nitric oxide, reactive cytokines, and free radicals) and hemodynamic responses, resulting in hypoxia-induced cerebral vasodilation leading to over perfusion of microvascular cerebral beds. This leads to intracranial hypertension with elevated capillary pressure and capillary leakage. The disruption of the blood-brain barrier from these stressors leads to subsequent vasogenic cerebral edema. Another theory is that hypoxia induces free radical formation, causing damage or failure of the Na+/K+ATPase pump with resultant astrocyte swelling from osmotic-oxidative stress and subsequent cytotoxic edema [29]. Similarly, hypoxia can cause cerebral edema in hanging patients. Steroids are indicated to treat vasogenic cerebral edema, whereas osmotic agents such as mannitol and hypertonic saline are preferred for the treatment of cytotoxic edema. The rationale for using dexamethasone in hanging-related cerebral edema is that it has demonstrated clinical benefit in conditions characterized predominantly by vasogenic cerebral edema, including bacterial meningitis and brain tumors [30].

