There is very limited evidence for the use of corticosteroid therapy in near-hanging. The existing literature is predominantly retrospective and comprises narrative reviews with several methodological limitations [8,18,31]. Our previous retrospective study demonstrated frequent empirical use of corticosteroid therapy in routine clinical practice but could not establish treatment efficacy because of its observational design [17]. No randomized controlled trials are currently available on steroid therapy specifically for near-hanging patients. However, there are studies available on steroid therapy for traumatic brain injury that closely resemble the type of brain injury seen in near-hanging cases. The MRC CRASH trial studied corticosteroids in patients with head injury, finding a higher death rate in those given corticosteroids (25.7%) compared with placebo (22.3%). This suggests that corticosteroids should not be used routinely to treat head injuries [19].

A narrative review by Kannamani et al [21] on near-hanging described head-end elevation, sedation, maintaining normocapnia (PaCO_2_ of 30‐35 mm Hg), and osmotic diuretics (hypertonic saline, mannitol) as management for cerebral edema and did not include steroid therapy in the management. A short review on steroid therapy in near-hanging patients reported that there is no evidence for or against the use of steroids in this situation [32].

Our CHANGING trial has been designed to address this evidence gap through a multicenter, randomized, double-blind, and placebo-controlled design. Random allocation and blinding of participants, treating clinicians, and outcome assessors are expected to minimize selection and assessment bias [22,28]. The study is conducted in 3 different tertiary care hospitals, which will improve external validity by including patients across diverse intensive care settings. To enhance the reliability of the study findings, the study follows a standardized treatment protocol, predefined neurological outcome, and systematic AE reporting [22].

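### Hospital stay is compared as raw duration with no rule for in-hospital death, so a mortality difference between arms would distort this secondary outcome

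*Protocol article*

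**What the plan says.** Under Objectives, a secondary aim is to "compare the length of hospital stay, and compare the incidence of in-hospital complications between the dexamethasone and placebo groups". Nothing there limits the comparison to survivors. Summary Statistics names only one continuous outcome: "The continuous dependent variable is the duration of hospital stay". Analytical Statistics then fixes the method. The sentence begins "For continuous outcomes, such as the duration of hospital stay, comparisons will be made using either the independent", and it names two candidates, Student's *t* and Mann-Whitney. Which of them applies, and what is reported, is settled as follows: "depending on data distribution, and the effect will be reported as an absolute difference between groups".

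The one rule for death stands under Outcome Assessment on Day 28: "Participants who die before day 28 will be assigned a GOS of 1 and will be included in the primary outcome analysis". It concerns the GOS. No section says how a death in hospital enters the stay comparison.

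Death is not a remote prospect. Expected Findings says that brain injury in near-hanging "is associated with substantial mortality and long-term neurological disability despite advances in critical care", and it cites a head-injury trial with mortality of 25.7% on corticosteroids and 22.3% on placebo.

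**The concern.** A hospital stay can end in discharge alive or in death, and raw duration does not tell the two apart. Followed as written, the analysis scores a death on day 2 as a 2-day stay, among the shortest values in the data, so a bad outcome counts as a favourable one.

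If mortality is equal in the arms, this does no systematic harm to the comparison. If it differs, the stay comparison carries part of the mortality difference, with a sign that depends on when the deaths occur. Early excess deaths on dexamethasone would read as a shorter stay. Early deaths prevented by dexamethasone would read as a longer stay, which would count against a drug that works.

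The other listed outcomes do not fully separate the two. Mortality is not itself a primary or secondary outcome, and the GOS dichotomy pools death with vegetative state and severe disability.

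**Working it through.** **The plan's own figure.** The article gives no expected value, SD or power for hospital stay, so there is nothing to reproduce for this outcome. The group size comes from Sample Size (75% vs 55%, 80% power, two-sided alpha taken as 0.05):

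n = (1.960 + 0.842)² × (0.75 × 0.25 + 0.55 × 0.45) / 0.20² = 85.4, so 86 per arm; 86 / 0.9 = 95.6, so 96 per arm and 192 in total. Both agree with the article.

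**Assumptions, not in the documents.** Stay in survivors is lognormal with median 7 days and log-SD 0.5, identical in both arms, so there is no true effect on survivors' stay. Time to death is exponential with mean 2 days, rounded up to whole days. There are 86 patients per arm. The mortality pairs are illustrative, except 25.7% vs 22.3%, which the article cites from head injury.

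**Shift in mean stay.** With equal stays in survivors,

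shift = (mortality on dexamethasone − mortality on placebo) × (mean stay of decedents − mean stay of survivors).

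Mean stay of survivors = 7 × exp(0.5²/2) = 7.93 days. Mean stay of decedents = 1 / (1 − exp(−1/2)) = 2.54 days. The second factor is therefore 2.54 − 7.93 = −5.39 days.

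The last column is from simulated trials analysed by Mann-Whitney at two-sided 5%, where the nominal chance of a significantly shorter stay is 2.5%.

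| Mortality, dexamethasone vs placebo | Shift in mean stay | Significantly shorter stay |
|---|---|---|
| 25.7% vs 22.3% | 0.034 × (−5.39) = −0.18 d | about 5% |
| 20% vs 15% | 0.05 × (−5.39) = −0.27 d | about 7% |
| 30% vs 15% | 0.15 × (−5.39) = −0.81 d | about 30% |

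With the arms exchanged (15% on dexamethasone, 30% on placebo), the shift is +0.81 days and the significant results fall in the direction of a longer stay at a similar rate.

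**Timing of death.** At 30% vs 15%, with mean time to death of 5, 7 and 10 days, decedents' mean stay after rounding up is 5.52, 7.51 and 10.51 days. The shift becomes 0.15 × (5.52 − 7.93) = −0.36, 0.15 × (7.51 − 7.93) = −0.06 and 0.15 × (10.51 − 7.93) = +0.39 days. The chance of a significantly shorter stay falls to about 12%, 5% and 2%.

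**A second set of assumptions.** With 96 per arm, survivors' median 8 days, decedents' median 2 days and log-SD 0.6 for both:
- 25.7% vs 22.3%: −0.24 days; significantly shorter in 6% (Mann-Whitney) or 5% (*t* test).
- 30% vs 15%: −1.06 days; 34% or 21%.
- 30% vs 15% with decedents' median 14 days: +1.06 days, so the sign reverses.
- Equal mortality: about 2 to 3%, so no bias.
- Death ranked as the worst stay: significantly shorter in 0 to 1% of trials in both unequal-mortality scenarios with early deaths; significantly worse in 6% (25.7% vs 22.3%) and 45% (30% vs 15%).

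**The case against.** Four objections carry weight.

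*Scope.* A condensed article may leave the scoring of deaths to an analysis plan that is not shown, and the Mann-Whitney option would allow death to be ranked worst. A reader might infer that the article says decedents are counted as short stays. It does not; that is what follows if the stated analysis is applied to raw durations. But the article does fix the variable, the tests and an absolute difference, and it does give a death rule for the GOS. The point is thus about a stated analysis, though a later rule could still settle it.

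*Size.* The 30% vs 15% scenario has no support in the article. Thirty percent mortality on dexamethasone exceeds the whole poor-outcome share of 25% planned for that arm, and the 23% among steroid recipients with GCS ≤13 in the retrospective study. At the only mortality contrast cited, the distortion is small. This objection stands. The mirror case (15% vs 30%) does fit within the planned poor-outcome shares of 25% and 45%.

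*Direction.* The article gives no timing of deaths, and it excludes patients in a "Moribund state where survival is deemed unlikely irrespective of intervention", which removes some early deaths. With later deaths the bias fades or reverses. This also stands.

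*Visibility.* A reader might infer that a lethal effect would be hidden or presented as a benefit. The documents do not support that. Death counts as poor in the GOS at day 28 and at discharge, deaths are serious adverse events, and the data and safety monitoring board reviews them. What remains is a misleading result on one secondary outcome.

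**Conclusion.** The concern holds in a limited form. The comparison of raw hospital stay has no rule for in-hospital death, in a population where the article itself expects substantial mortality, and it is distorted whenever mortality differs between arms and deaths do not fall at about the usual time of discharge.

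Under the 7-day and 2-day assumptions, the distortion runs from about −0.2 days and a 5% chance of a significantly shorter stay (nominal 2.5%) at the cited mortality contrast to about −0.8 days and 30% at a doubling of mortality. These figures rest on assumed stays, timing and, except for the cited pair, mortality. The sign is not fixed: it depends on which arm has more deaths and on how early they occur. The primary outcome is not affected. The gap is worth closing because the remedy is cheap and the stated method has no protection against it.

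**What to change.** Keep hospital stay as the secondary outcome and state one rule for death:

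- Make the between-arm test a rank comparison in which in-hospital death is ranked as the worst result, or analyse time to discharge alive with death as a competing event. Stratify either by the GCS randomisation stratum (≤8, >8).
- Show raw stay in survivors as description only, without a test, beside all-cause mortality to day 28 by arm.
- Days alive and out of hospital to day 28 (death = 0) is an alternative, but only if readmission dates are recorded at the day-28 contact. The article describes that contact as assessing the GOS and does not say that readmissions are collected.

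**Cost.** The first two items need analysis wording only: duration of stay, final hospital outcome and day-28 status are already collected. Three patients were enrolled at submission, so the rule can be set well before the interim look at 50% enrolment. The small downside is that the measure is less familiar than a mean difference in days; an absolute difference in days would then serve only for the descriptive display.
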